#### **4.3 Study Procedures**

Approximately 150 healthy female subjects with FSIAD will be enrolled in the study. After written informed consent has been obtained and inclusion and exclusion criteria have been met, subjects will be enrolled in the study. An overview of the study visits is provided in Table 1; a detailed schedule of the study procedures is provided in Appendix 2.

**Table 1: Overview of Study Visits**

| Study Visit           | Assessment (Duration)            |
|-----------------------|----------------------------------|
| Visit 0               | Screening (3 hours)              |
| Visit 1               | Start-up visit (1,5 hour)        |
| Visits 2, 3, 4, and 5 | Study regimen follow-up (1 hour) |
| Visits 6              | Final follow-up (1 hour)         |

#### **4.3.1 Placebo Run-in Period**

All subjects will begin the study with a 2-week single blind, placebo run-in period, before starting the double-blind treatment period. The placebo run-in period is organized exactly the same as the treatment period and is intended to minimize possible placebo effects.

#### **4.3.2 Visits**

##### **4.3.2.1 V0: Screening Visit**

Written informed consent will be obtained prior to any enrollment procedure.

The screening visit (V0) will include the following (not necessarily in this order, except giving informed consent which must always be done first):

1. Giving written informed consent
2. Interview with experienced psychologist/appropriately trained healthcare provider to assess sexual history and diagnose FSIAD with or without female orgasmic disorder .
3. Assessment of alcohol consumption and smoking history
4. Physical examination, including medical, gynecological, and surgical history, vital signs (including supine blood pressure and heart rate), 12-lead ECG (supine), monitoring for signs of hyperandrogenism (see Section 4.3.8.2)
5. Collection of blood sample for routine hematology, chemistry, steroid hormone levels, and serology (Appendix 3)
6. Urine drug screening (Section 4.3.6)
7. Routine urinalysis (Section 4.3.6.1)
8. Urine pregnancy test
9. Completion of the following questionnaires: Sexual Anamnesis Questionnaire-Diagnostic (SAQ-D), Sexual Motivation Questionnaire (SMQ), Female Sexual Distress Scale revised (FSDS-R)

**Table 2: Measurements and Activities at V0**

---

**V0: Enrollment/Screening**

---

Written informed consent  
Inclusion/exclusion criteria  
Demographics  
Medical history  
Interview psychologist/trained healthcare provider  
Height  
Body weight  
Vital signs, ECG  
Physical examination  
Hyperandrogenism monitoring  
Pregnancy test  
Urine drug screen  
Urinalysis: dipstick  
Hematology and chemistry assessment  
Questionnaires: SAQ-D, SMQ, FSDS-R  
Concomitant medications

SAQ-D = Sexual Anamnesis Questionnaire-Diagnostic; SMQ = Sexual Motivation Questionnaire ;  
Female Sexual Distress Scale revised (FSDS-R)

If a subject is not enrolled for CD001 within 12 weeks after screening (V0) but is still eligible for inclusion consideration, the subject must have initial safety lab work repeated; chemistry, hematology, and hormone levels. Additionally, any other changes from baseline in the subject's health will be documented (see Table 3 for details).

**Table 3: Measurements and Activities >12 weeks after screening**

---

**V0: Rescreening**

---

Update Inclusion/exclusion criteria  
Update Demographics  
Update Medical history   
Pregnancy test (women of child-bearing potential)  
Update Interview psychologist/trained healthcare provider   
Hematology, chemistry, and hormones assessment

Questionnaires: SAQ-D, FSDS-R, SMQ 

Update Concomitant medications 

SAQ-D = Sexual Anamnesis Questionnaire-Diagnostic;; SMQ = Sexual Motivation Questionnaire;  
Female Sexual Distress Scale revised (FSDS-R)

- 1 Check the medical history for significant and/or relevant changes or events (e.g., Urinary Tract Infection (UTI); recent surgery); in case of any event or change please repeat the appropriate screening measurements and/or activities (e.g. physical- ,or gynecological examination, urinalysis).
- 2 Check if subjects have had significant change in sexual functioning (e.g. due to life event).
- 3 If subjects report change in sexual functioning, SAQ-D, FSDS-R and SMQ must be filled out again.
- 4 Check if subjects concomitant medication has changed (e.g. because of UTI, recent surgery).

#### 4.3.2.2 V1: Start-up Visit

During the start-up visit (V1), subjects will be examined for clinically significant deviations from normal in vital signs. AEs (as defined in Section 5) and concomitant medications will be recorded, monitoring for signs of hyperandrogenism and a urine pregnancy test will be done for all women of child-bearing capability. Also a hand scan of the left hand will be made to measure digit length. The subject will see a psycho-educational DVD with theoretical background information about sexual functioning and fantasizing exercises. After watching the DVD the information will be discussed with a psychologist or similar healthcare provider. Instructions will be given on how to complete the SED and the weekly diary. Subjects will fill out the FSDS-R questionnaire. The first medication bottle will be dispensed to subjects. A blood sample will be taken for the assessment of the biological markers (CAG repeat length of the androgen receptor (AR) gene, SERT, 5-HT1a genotype, and several other markers using microarray chips) if these results are not current within past 12 months and obtainable as part of medical history.

Subjects are expected to complete the full two (2) weeks of the placebo run in period before participating in Visit 2. Subjects may be scheduled for V2 from one day after the end of the placebo run in period and up to one (1) week after the end of that period.

**Table 4: Measurements and Activities at V1**

#### V1: Start-up Visit

|                                                                  |
|------------------------------------------------------------------|
| Inclusion/exclusion criteria                                     |
| Pregnancy test                                                   |
| Psychoeducational DVD                                            |
| 2D:4D measurement, left hand                                     |
| Vital signs                                                      |
| Collection of blood samples for assessment of biological markers |
| Hyperandrogenism monitoring                                      |

---

**V1: Start-up Visit**

---

Instructions for SED and weekly diary

Study medication dispensinga

Concomitant medications

Adverse and serious adverse events

Questionnaires: FSDS-R

Randomisation (prior to V1)

---

Notes: ; FSDS-R=Female Sexual Distress Scale –Revised; SED= Sexual Event Diary;

a Study medication dispensed at V1, V2, V3, and V4.

**4.3.2.3 V2, V3, V4, and V5: Study Regimen Follow-up Visits**

During the study regimen follow-up visits (V2, V3, V4, and V5), subjects will be examined for clinically significant deviations from normal in vital signs. Any AEs and use of concomitant medications will be recorded, monitoring for signs of hyperandrogenism and a urine pregnancy test will be done for women of child bearing potential. During the study regimen follow-up visits, subjects will fill out the FSDS-R, PGI-I and PBE questionnaires and the psychologist/designee will conduct an interview to assess improvement. At visit 1, 2, 3, and 4 subjects will receive medication for 2 weeks.

The visits should be scheduled from one (1) day after the end of the 2-week treatment period up to three (3) weeks after the end of that period (see Appendix 1: Study Timelines and Windows).

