##### **3.3.2 Exploratory Endpoints**

- Change from placebo in experienced sexually-related personal distress, measured by the Female Sexual Distress Scale-Revised (FSDS-R), specifically item 13.
- Evaluation of meaningful improvement during treatment period, measured by the single item Patient's Global Impression of Improvement (PGI-I)
- Evaluation of meaningful benefit of study medication during treatment period, measured by the single item Patient Benefit Evaluation (PBE)
- Change from placebo in frequency of orgasms, following medication intake, measured by the SED
- Change from placebo in sexual desire, following medication intake, measured by the SED
- Change from placebo in physical arousal, following medication intake, measured by the SED
- Change from placebo in mental arousal, following medication intake, measured by the SED
- Change from placebo in sexual pleasure, following medication intake, measured by the SED

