**4.3.2.5 Home: On-going Measurements**

Subjects will be required to fill out 2 kind of diaries, a weekly diary (Section 4.3.4.2) and the SED (Section 4.3.4.3), accessing a secure website using a home computer. The weekly diary is a

structured questionnaire that has to be completed once a week. The SED is a questionnaire that has to be completed within 24 hours of a sexual event (this includes masturbation). Subjects are requested to have at least two sexual events a week.

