#### **4.3.4.6 Patient's Global Impression of Improvement (PGI-I)**

The PGI-I is used to determine if the subject feels that she has experienced any meaningful improvement during the treatment period (Appendix 14).

"How is your condition – meaning decreased sexual desire and feeling bothered by it – today compared with when you started study medication?" [very much improved 1 to 7 very much worse]

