#### **4.3.4.7 Patient Benefit Evaluation (PBE)**

The PBE is used to determine if the subject feels that she has had any meaningful benefit of the study medication (Appendix 15).

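### The PGI-I rates a day after the regimen has ended although its endpoint is improvement during treatment, and the same 1-to-21-day visit lag adds off-drug days or recall error to FSDS-R and PBE

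*Protocol*

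**What the plan says.** Protocol Section 4.3.2.3 states that at V2, V3, V4 and V5 "subjects will fill out the FSDS-R, PGI-I and PBE questionnaires". The same section has those visits "scheduled from one (1) day after the end of the 2-week treatment period up to three (3) weeks after the end of that period" and refers to Appendix 1 for the windows.

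The exploratory endpoints in Section 3.3.2 are:

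- **PGI-I:** "Evaluation of meaningful improvement during treatment period".
- **PBE:** "Evaluation of meaningful benefit of study medication during treatment period".
- **FSDS-R:** "Change from placebo in experienced sexually-related personal distress, measured by the Female Sexual Distress Scale-Revised (FSDS-R), specifically item 13".

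The PGI-I item is given in Section 4.3.4.6. It asks how the condition is "today compared with when you started study medication". Section 4.3.4.7 says the PBE is "used to determine if the subject feels that she has had any meaningful benefit of the study medication"; the item itself is not reproduced. No recall period for the FSDS-R appears in the text at hand.

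The weekly diary and the Sexual Event Diary (SED) are completed at home, "accessing a secure website using a home computer" (Section 4.3.2.5).

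**The concern.** All three forms are tied to visits that, by rule, come after the 2-week regimen has finished. Under Section 4.1.1 the tablets are taken partly on demand, with 8 supplied per regimen and no resupply. Section 2.1.3 describes effects about four hours after intake, and Section 3.4 sets a minimum washout of 2 days. An answer about the present day, given up to three weeks later, is therefore not plainly an answer about the regimen.

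Each visit has its own window, so a woman's Lybrido, Lybridos and placebo answers can be given at different lags. The FSDS-R is the only distress measure among the listed endpoints, and PGI-I and PBE are the only global patient judgements. Analysis cannot recover an end-of-regimen answer that was never collected.

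**Working it through.** The plan gives no numerical result for this point, so the check is date arithmetic plus a comparison of each item with its endpoint.

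**Inputs.** Regimen length is 14 days and minimum washout 2 days (Section 3.4). The V2 to V5 window is 1 to 21 days after regimen end (Section 4.3.2.3). The V2 window is also given as 1 day to 1 week after the run-in (Section 4.3.2.2). Planned visits are V1 at week 0 and V2 to V5 at weeks 2, 4, 6 and 8, with no window shown (Appendix 1). V6 is 1 week after V5, plus or minus 1 week (Section 4.3.2.4).

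**1. Lag after the regimen.** A visit g days after regimen end falls on day 14 + g from regimen start.

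| g (days) | Visit day | g / 14 |
|---|---|---|
| 1 | 15 | 0.07 |
| 7 | 21 | 0.50 |
| 14 | 28 | 1.00 |
| 21 | 35 | 1.50 |

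Of the 21 permitted days, days 3 to 21 lie beyond the 2-day minimum washout: 19 of 21.

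**2. Overlap with follow-up.** A woman whose V5 is on day 1 has V6 nominally on day 1 + 7 = 8 off drug. Another woman's V5 may be on day 21. One woman's follow-up FSDS-R can thus be closer to treatment than another's end-of-regimen FSDS-R.

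**3. PGI-I.** The item rates the day of completion. At V3 to V5 that day is after the double-blind regimen, whereas the endpoint is improvement during treatment. The comparison point is the start of study medication, which is first dispensed at V1 for the placebo run-in, so it is not specific to a regimen. The look-back at V5, if each period starts at the preceding visit, is:

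- On schedule: 4 × 2 = 8 weeks, which reproduces Appendix 1.
- All windows used in full, V2 limited to 1 week: (2 + 1) + 3 × (2 + 3) = 18 weeks.
- All windows used in full, V2 allowed 3 weeks: 4 × (2 + 3) = 20 weeks.

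**4. FSDS-R.** The recall period is not shown, so these are assumed values. If recall covers the R days before the visit, it contains no regimen day once g exceeds R.

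- R = 7: days 8 to 21, or 14 of 21 permitted days (67%), contain no regimen day.
- R = 30: some regimen days are always included. A day-1 visit covers the 14 regimen days plus 16 earlier days; with a 2-day washout, 16 − 2 = 14 of those belong to the preceding period. A day-21 visit covers 20 off-drug days and 30 − 20 = 10 regimen days.

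These count permitted days, not expected visits.

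**5. PBE.** Section 4.3.4.7 describes a judgement looking back on benefit from the medication. A later visit lengthens the recall; it does not by itself move the judgement off the regimen.

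**The case against.** The strongest case on the other side has five parts.

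- **Only one item is shown.** Of the three, only the PGI-I wording is in the text. A reader might infer that all three forms fail to measure the regimen. The documents do not support that: the PBE is described as retrospective, and the FSDS-R recall period is unknown. The FSDS-R is also completed at V0, V1 and V6, not only at V2 to V5. This stands.
- **Undosed days occur within the regimen too.** With at most 8 doses in 14 days, taken one a day, at least 14 − 8 = 6 days carry no dose; at the required minimum of 4 doses, at least 10. The PGI-I asks about a condition, not the response hours after a tablet, and a visit on day 1 differs little from the last regimen day. This softens the PGI-I point at the near end of the window but not at the far end.
- **No bias is derived.** A reader might infer that drug-placebo differences must shrink toward zero, or that they partly reflect visit timing. Shrinkage is plausible, but the documents provide nothing to size it. All regimens share one window under double-blind, randomised order, and nothing suggests that the lag differs systematically by treatment. Added noise is what can be claimed.
- **The far limit is not the plan.** Appendix 1 schedules visits every two weeks, so 21 days is an outer bound. This stands.
- **The endpoints are exploratory.** Section 6.3 gives them summary statistics only. This stands and limits the weight of the point.

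**Conclusion.** The point holds in a limited form. The PGI-I, as worded and timed, does not match its endpoint: at V3 to V5 it rates a day 1 to 21 days after the regimen, against a starting point 8 weeks earlier at V5 on schedule and 18 or 20 weeks earlier at the window limits. For FSDS-R and PBE, the variable lag adds off-drug days or recall error, and it adds noise to the within-woman FSDS-R change from placebo. How much depends on a recall period and item wording not in the text at hand; the 67% figure holds only under an assumed 7-day recall.

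No decision or hypothesis test in the protocol rests on these three measures. The primary endpoint and the other SED-based endpoints are unaffected, because the SED is completed at home within 24 hours of a sexual event. This is an inexpensive improvement, not a threat to the trial's main conclusion.

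The V2 window is a separate inconsistency: one week in Section 4.3.2.2, three weeks in Section 4.3.2.3, and absent from Appendix 1, which Section 4.3.2.3 cites for it.

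**What to change.** Have FSDS-R, PGI-I and PBE completed on the last day of each 2-week regimen, within a short stated completion window, on the secure website already used for the SED and weekly diary. Keep the clinic visit for safety and dispensing. The day rated by the PGI-I then belongs to the regimen, and the lag is nearly equal across a woman's three regimens.

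The instruments' standard wording can stay. Rewording the PGI-I to refer to the past two weeks is possible, but it departs from the standard item and is not needed once the timing is fixed. The start-of-medication comparison point remains common to all regimens. Shortening the visit window alone would reduce the lag but still leave the forms after the regimen.

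The cost is one extra home entry per regimen on an existing platform, with matching edits to Section 4.3.2.3, Table 5 and Appendix 2. Sections 4.3.2.2 and 4.3.2.3 and Appendix 1 should also be reconciled so that a single V2 window is stated.

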**Table 5: Measurements and Activities at V2, V3, V4, and V5**

---

**V2, V3, V4, and V5: Regimen Follow-up**

---

Inclusion/exclusion criteria

Pregnancy test

Vital signs

Hyperandrogenism monitoring

Interview psychologist/sexologist

Concomitant medications

Adverse and serious adverse events

Study medication dispensinga

Study medication interim countb

Questionnaires: FSDS-R, PGI-I and PBE

---

**V2, V3, V4, and V5: Regimen Follow-up**

---

Notes: FSDS-R= Female Sexual Distress Scale –Revised; PBE = Patient Benefit Evaluation; PGI-I = Patient’s Global Impression of Improvement

a Study medication dispensed at V2, V3, and V4.

b Study medication interim count at V3, V4, and V5

**4.3.2.4 V6: Final Follow-up Visit**

During the final follow-up visit (V6), subjects will receive a physical examination and will be assessed for clinically significant deviations from normal in vital signs; a blood sample will be collected for hematology and clinical chemistry assessments (Appendix 3). Any AEs and use of concomitant medications will be recorded, monitoring for signs of hyperandrogenism and a urine pregnancy test will be done for women of child bearing potential. Subjects will fill out the FSDS-R, and the psychologist/designee will conduct an interview to assess improvement. Visit 6 should be scheduled one (1) week after completion of Visit 5, +/- one (1) week.

**Table 6: Measurements and Activities at V6**

---

**V6: Final follow-up**

---

Interview psychologist/sexologist  
Physical examination  
Body weight  
Pregnancy test  
Vital signs  
Hyperandrogenism monitoring  
Hematology safety  
Clinical chemistry safety  
Concomitant medications  
Adverse and serious adverse events  
Questionnaires: FSDS-R

---

Notes: ; FSDS-R= Female Sexual Distress Scale –Revised;

**4.3.2.5 Home: On-going Measurements**

Subjects will be required to fill out 2 kind of diaries, a weekly diary (Section 4.3.4.2) and the SED (Section 4.3.4.3), accessing a secure website using a home computer. The weekly diary is a

structured questionnaire that has to be completed once a week. The SED is a questionnaire that has to be completed within 24 hours of a sexual event (this includes masturbation). Subjects are requested to have at least two sexual events a week.

### **4.3.3 Description of Measurements**

#### **4.3.3.1 Hand Scan Measuring Digit Ratio**

Subjects will be asked to remove any jewelry or rings that would interfere with obtaining finger length measurements (subjects who are unable to remove rings will be asked to slide the jewelry up the digit as far as possible to allow documentation of the digit/hand intersection). Each subject's left hand will be scanned using a standard photo scanner at a resolution of 200 dpi. The subject will be instructed to place the ventral surface of their hand lightly on the surface of the scanner, with the second to fifth fingers held parallel and the tip of the middle finger aligned with the wrist and elbow. Scanned hand images will be analyzed using computer-assisted image analysis software. A built-in measurement tool (accurate to 0.1 mm) will be used to measure digit length. The length of the second and fourth digit of the left hand will be measured from the ventral proximal crease of the digit to the tip.

### **4.3.4 Questionnaires**

#### **4.3.4.1 Sexual Anamnesis Questionnaire-Diagnostic**

The SAQ-D is a 43-item self-report questionnaire (Appendix 4). It is designed to assess the different aspects of sexual functioning (desire, arousal, orgasm, and pain corresponding to the DSM-IV-TR), presence of childhood sexual abuse, quality of partner relationship, and the presence of comorbidity factors. Several items of this questionnaire are used in the demarcation formula.

#### **4.3.4.2 Weekly Diary**

Subjects will be instructed to fill out the weekly diary once a week (Appendix 6). This self-report questionnaire includes 7 multiple choice questions concerning sexual desire, arousal, and inhibition felt during the past week.

#### **4.3.4.3 Sexual Event Diary**

The SED is a self-report questionnaire (Appendix 7). It is designed to assess the sexual satisfaction of a recent sexual event. Subjects are instructed to fill out the SED within 24 hours of any sexual event they experience.

#### **4.3.4.4 Sexual Motivation Questionnaire**

The SMQ is a 40-item self-report trait questionnaire using 5-point Likert scale items (Appendix 11). This questionnaire assesses specific aspects of sexual motivation. Several items of this questionnaire are used in the demarcation formula.

#### **4.3.4.5 Female Sexual Distress Scale –Revised**

The Female Sexual Distress Scale –revised is a 13-item standardized, quantitative scale (Appendix 12). This questionnaire measures sexually-related distress in women.

#### **4.3.4.6 Patient's Global Impression of Improvement (PGI-I)**

The PGI-I is used to determine if the subject feels that she has experienced any meaningful improvement during the treatment period (Appendix 14).

"How is your condition – meaning decreased sexual desire and feeling bothered by it – today compared with when you started study medication?" [very much improved 1 to 7 very much worse]

#### **4.3.4.7 Patient Benefit Evaluation (PBE)**

The PBE is used to determine if the subject feels that she has had any meaningful benefit of the study medication (Appendix 15).

#### **4.3.5 Program for psycho-education**

The program for psychological counseling will be carried out by digital versatile disk (DVD).

The DVD contains a 30-minute interview with an experienced psychologist. Topics include sexual functioning and the female response cycle, bodily changes during sexual arousal, differences between men and women, problems in sexual functioning, and misunderstandings. There is also a 7-minute training module on sexual fantasizing.

The entire DVD will only be shown at Visit 1. Afterwards, the subject and the psychologist will discuss the psycho-educational parts.

